### Futility criteria

We applied the futility criteria based on ELSO guideline, ARREST trial and German consensus [8, 11, 20], and these criteria must be met in combination ($$\ge$$ 2) to consider futility. The criteria include: 1. End-tidal CO2 < 10 mmHg, 2. PaO2 < 50 mmHg despite maximal ventilation, 3. Serum lactate > 20 mmol/L.

#### Post resuscitation protocol

After initial stabilization at ED, electrocardiography and echocardiography would be arranged to identify cardiac causes for OHCA. Computed tomography would be arranged (either before or after cath intervention) to exclude non cardiac causes of OHCA or contraindication (Table 1). All patients without contraindications for coronary intervention will then be transferred to the cardiac catheterization laboratory (CCL) for coronary angiography. With successful emergent management, patients are admitted to the cardiac ICU for continued post-cardiac arrest care.

#### Intervention—ECMO initiation

After randomization, if the enrolled patient has stable ROSC before initiating ECMO, he/she will be transferred to the cardiac catheterization laboratory (CCL) without ECMO support. The indications for ECMO include no ROSC or unstable ROSC (persistent or recurrent VF or pVT, profound cardiogenic shock with systolic blood pressure (BP) < 90 mmHg or mean BP < 60 mmHg despite intense inotropic support (bolus of epinephrine > 3 bolus), or persistent hypoxia with arterial oxygen saturation (SaO2) < 90% despite maximal ventilation support). The femoral artery and vein access will be cannulated under ultrasound guidance. ECMO would be deemed futile if more than one discontinuation criterion suggesting ineffective resuscitation (end-tidal carbon dioxide < 10 mmHg, partial pressure of oxygen in arterial blood < 50 mmHg or oxygen saturation < 85%, or serum lactate > 20 mmol/L) has been met.

However, if unstable ROSC persists as defined above, ECMO is initiated according to the randomization arm protocol. For the emergency total ECLS group (Fig. 1), the veno-arterial ECMO (VA-ECMO) will be initiated within 15 min after randomization. For standard ACLS with the recue ECMO group, patients will receive 15 min of ACLS at ED first. If there is no stable ROSC, the futility of ECLS would be reevaluated. Therefore, the recue VA-ECMO should be initiated after 15 min since randomization.

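### The futility rule for ECMO is written twice with different oxygen criteria, so some patients are futile under one section and not under the other

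*Protocol article*

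**What the plan says.** The section Futility criteria gives three numbered items and says that "these criteria must be met in combination", with two or more required before futility is considered. The items are "End-tidal CO2 < 10 mmHg", "PaO2 < 50 mmHg despite maximal ventilation" and "Serum lactate > 20 mmol/L".

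The section Intervention—ECMO initiation states the rule again: "ECMO would be deemed futile if more than one discontinuation criterion suggesting ineffective resuscitation" is met. Its list has "end-tidal carbon dioxide < 10 mmHg", then "partial pressure of oxygen in arterial blood < 50 mmHg or oxygen saturation < 85" (per cent), then the same lactate limit of 20 mmol/L. The oxygen item there has no condition about maximal ventilation.

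The same section says that in the standard ACLS arm futility is assessed again after 15 minutes of ACLS, if there is no stable ROSC and before rescue ECMO. Neither section refers to the other or says which list applies.

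**The concern.** The required count, the CO2 limit and the lactate limit all match, so these are plainly meant to be one rule. The oxygen item differs in two respects: the second statement adds a saturation limb, and it omits the ventilation condition. Both statements are current text with explicit thresholds, so a team can follow either one and be following the protocol.

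The rule bears on whether a patient receives ECMO, the treatment whose timing the trial tests. The trial is open-label and runs in eight centres. If teams or hospitals work from different lists, similar patients can be handled differently at a step close to death and hence to the primary endpoint. All enrolled patients are analysed primarily by intention to treat, so the consequences stay in the primary comparison.

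**Working it through.** The protocol states no figure that could be reproduced here. The check is whether the two rules can give different answers, and for whom.

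**Inputs.** Five yes/no facts (1 = yes, 0 = no), with limits from the two sections:

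- C: end-tidal CO2 below 10 mmHg
- P: PaO2 below 50 mmHg
- V: ventilation already maximal
- S: oxygen saturation below 85%
- L: lactate above 20 mmol/L

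**Rules.**

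- Rule A (Futility criteria): C + (P × V) + L ≥ 2
- Rule B (Intervention—ECMO initiation): C + max(P, S) + L ≥ 2

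**Direction.** P × V can never exceed max(P, S). Every patient futile under A is therefore futile under B, and disagreement can only run from not futile (A) to futile (B).

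**Count over the 2⁵ = 32 combinations.**

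| | Rule A futile | Rule B futile |
|---|---|---|
| C + L = 2 (1 way), oxygen irrelevant | 1 × 8 = 8 | 1 × 8 = 8 |
| C + L = 1 (2 ways), oxygen item needed | 2 × 2 = 4 | 2 × 6 = 12 |
| C + L = 0 (1 way) | 0 | 0 |
| Total | 12 | 20 |

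The rules disagree in 20 − 12 = 8 combinations, all with exactly one of C and L present. For each of those 2 ways there are 4 oxygen patterns that disagree: P = 0 with S = 1 (V either way, 2 patterns) and P = 1 with V = 0 (S either way, 2 patterns). That gives 2 × 4 = 8.

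**Each difference matters alone.** If the ventilation condition is ignored, 16 combinations remain. Rule A then gives 4 + 2 × 2 = 8 futile and rule B gives 4 + 2 × 3 = 10, so 2 still differ, both because of the saturation limb. If the saturation limb is ignored instead, 2 of 16 differ: P = 1, V = 0 and exactly one of C and L.

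**Two illustrative patients (values assumed).**

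| | Patient 1 | Patient 2 |
|---|---|---|
| PaO2 | 55 mmHg | 45 mmHg, ventilation not yet maximal |
| Saturation | 82% | not needed |
| Lactate | 22 mmol/L | 22 mmol/L |
| End-tidal CO2 | 15 mmHg | 15 mmHg |
| Criteria met, rule A | 1 (not futile) | 1 (not futile) |
| Criteria met, rule B | 2 (futile) | 2 (futile) |

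Patient 1 assumes that a saturation below 85% can occur with PaO2 of at least 50 mmHg. The documents do not give that relation, though listing saturation as an alternative suggests it was meant to add something. Patient 2 needs no such assumption.

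**The case against.** The strongest reply is that this is one limb of an otherwise matching rule, with no evidence that many patients fall in the gap. That stands as a limit on severity. The 8 of 32 counts logical combinations and says nothing about frequency.

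The text is also softer than a mandatory stop. One section speaks of considering futility and the other of deeming ECMO futile; neither spells out withholding or stopping. The claim should therefore be that the rule bears on receipt of ECMO, not that each reclassified patient is certainly denied it.

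A reader might infer more from the same text. Three such readings are not supported:

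- **Low saturation is both a reason for ECMO and a reason against it.** The indications include "persistent hypoxia with arterial oxygen saturation (SaO2) < 90% despite maximal ventilation support", so the two lists overlap. That is not a contradiction. Futility is asked about patients for whom ECMO is in question, and low saturation alone does not reach two criteria.
- **Low oxygen alone makes a patient futile.** This needs PaO2 and saturation to count as two separate criteria; 3 of 16 combinations would then differ, ventilation set aside. The sentence joins them as one item, and the other section numbers exactly three criteria with one for oxygen. Separate counting is a strained reading, though one clarifying phrase would close it off.
- **The discrepancy favours one arm.** Neither version is tied to an arm. The first section is general, and the second gives its list before the arm-specific text. The 15-minute reassessment in the standard ACLS arm is a matter of timing, not of which list applies.

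None of this removes the conflict in the oxygen item.

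**Conclusion.** The point holds as an internal inconsistency: two operative versions of one futility rule, with the version in Intervention—ECMO initiation always the broader. They part for patients with exactly one of low end-tidal CO2 or high lactate who also have either saturation below 85% with PaO2 of at least 50 mmHg, or PaO2 below 50 mmHg before ventilation is maximal.

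The share of patients affected cannot be computed, because the documents give no distribution of these values. A reader might assume a share, say 5% of the control arm, and set it against the planned difference of 25 − 12 = 13 points. That compares a share of patients with a difference in outcome rates. Even granting the assumed 5%, and supposing that all of them lost the outcome they would otherwise have had at the planned control rate of 12%, the arm would lose 0.05 × 12 = 0.6 points; at the 25% planned for the ECLS arm, 0.05 × 25 = 1.25 points. Both figures assume average prognosis, although each of these patients also meets another criterion that the protocol takes to suggest ineffective resuscitation.

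This should be corrected because it concerns the trial's key treatment and the text is wrong as written. It does not rest on a demonstrated shift in the primary result.

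**What to change.** Reconcile Futility criteria and Intervention—ECMO initiation to a single list, stated once and referred to elsewhere, and used at every futility assessment, including the one after 15 minutes of ACLS in the standard arm. The list should settle three things:

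- whether a saturation limb belongs in it;
- whether the maximal-ventilation condition applies, and to which items;
- whether the oxygen item counts once or otherwise.

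Which criteria and limits to use is for the investigators to decide; this review takes no position on that.

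The cost is a wording change in two sections. It does not touch the sample size, the randomization or the analysis model.

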#### LV unloading in ECMO-supported patients

During ECMO support, active left ventricular (LV) unloading by balloon atrial septostomy, direct left atrial venoarterial (LAVA) cannulation, Impella®, percutaneous LV/pulmonary artery venting, would be considered when LV global akinesia, absence of aortic valve opening, or spontaneous echocardiographic contrast within LV is demonstrated by echocardiography, or frothy sputum with pulmonary congestion is present, or pulse pressure < 10 mmHg, or elevated left ventricular end-diastolic pressure $$\ge$$ 30 mmHg (Table 2).

**Table 2 Tab2:** Criteria and indications for active left ventricular (LV) unloading

1. Persistent refractory VF/VT even after ECMO
2. Non-opening aortic valve
3. Pulse pressure < 10 mmHg
4. Severe LV dilatation/global hypokinesia
5. Severe pulmonary edema with frothy sputum
6. LVEDP $$\ge$$ 30 mmHg
7. “Smoke” image in LV, spontaneous echocardiographic contrast

ECMO: extracorporeal membrane oxygenation; LV: left ventricle; LVEDP: left ventricular end-diastolic pressure; VF: ventricular fibrillation, VT: ventricular tachycardia

### Post-cardiac arrest care protocols

#### Targeted Temperature Management (TTM)

Target temperature of 33–36 °C for 24 h, followed by controlled rewarming at 0.25–0.5 °C per hour for those without rescue ECMO. For the ECMO-supported victim, prevention of hyperthermia (> 37 °C) is warranted, intentional hypothermia is not mandatory according to the policy for individual centers. Prevention of shivering with neuromuscular blockade was administrated if needed. When the patient becomes agitated after resuscitation, the midazolam and analgesia with fentanyl will give for sedation.

#### ECMO management (in rescue ECMO)

The target flow rate of ECMO was kept around 60–80 mL/kg/min, and the anticoagulation: unfractionated heparin targeting a PTT 50–70 s. Complication of ECMO (limb ischemia, bleeding, thrombosis, etc.) was carefully monitored, recorded and reported in the case report form (CRF) [8].

#### Hemodynamic targets

The mean arterial pressure are maintained around 65–75 mmHg, and the central venous oxygen saturation: > 70%. The lactate level was monitored as regular fashion.

#### Mechanical ventilation

We apply the lung-protective ventilation with tidal volume 6–8 mL/kg ideal body weight, the plateau pressure < 30 cmH_2_O, titrated to maintain saturation over 90%.

#### Neuroprognostication

Neuroprognostication will be determined at least 5–7 days after Return of Spontaneous Circulation (ROSC) for patients who received Targeted Temperature Management (TTM). This timing ensures sufficient clearance of sedatives and resolution of potential drug effects or reversible physiological abnormalities before any prognosis is established. The assessment will occur approximately 72 h after the patient has reached normothermia following the TTM period. This timing ensures sufficient clearance of sedatives and resolution of potential drug effects or reversible physiological abnormalities before any prognosis is established.

The use of sedatives may affect the evaluation of the assessment of neurological status. We prioritize protocol to minimize the lingering effect of sedation. The clinical practice is discontinuation of sedation 72 h before assessment.

Prognostication utilizes a multi-modal approach incorporating multiple clinical and objective tests, such as neuroimages (CT and/or MRI) and biomarkers [21]. Not a single information determine the decision-making.

### Withdrawal-of-Care (WLST)

#### Criteria

Decisions regarding WLST are made only after the **c**ompletion of the multi-modal neuroprognostication protocol confirms an irreversible, devastating neurological prognosis.

Standardized Criteria: Criteria for poor prognosis leading to potential WLST are standardized across all centers and must include conclusive evidence from 2 to 3 modalities indicating a near-zero probability of functional recovery. These criteria include: (1)Persistent coma without brainstem reflexes on neurological exam, (2) Diffuse, severe anoxic injury on MRI/CT, (3)Burst suppression or status epilepticus refractory to treatment on EEG.

Decision made by multidisciplinary team after comprehensive neuroprognostication, and consultation about the goal of care under Shared decision making (SDM) process [21].

#### Follow-up

All enrolled patients will be followed at hospital discharge and 1 month, 3 months, and 6 months after discharge. Survival status, neurological and functional recovery, readmission, and causes of death or readmission will be assessed via periodic interview or scheduled outpatient appointment (Fig. 2).

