**Fig. 2 Fig2:**
[figure not shown]
Timeline of post-resuscitation management and follow-up. This schematic outline illustrates the temporal progression of key clinical interventions following ROSC or initiation of ECLS. Early actions such as coronary angiography, targeted temperature management, and LV unloading might occur within the first days. Intermediate evaluations, including clinical examination, and EEG or MRI in patients who remain comatose, are emphasized at least 5–7 days after ROSC. Clinical examination will be assessed at 30 days, 90 days and 180 days after cardiac arrest. Long-term strategies incorporating GDMT, device therapy or advanced therapy might be considered for survivors with heart failure. CPC: cerebral performance category; ECLS: extracorporeal life support; EEG: electroencephalogram; GDMT: guideline-directed medical therapy; LV: left ventricular; MRI: magnetic resonance imaging; mRS: modified Rankin scale; ROSC: return of spontaneous circulation

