#### Study endpoints

The primary endpoint is defined as 30-day survival with Cerebral Performance Category (CPC) score of 1 or 2). The CPC score will be assessed by the designated neurologists at each participant hospital, who are blinded to the intervention received. Secondary endpoints include favorable neurological status (modified Rankin scale (mRS) < 3, crude survival and neurologically favorable survival at discharge, 3 months, and 6 months; duration of mechanical ventilation; duration of stay in ICU; duration of hospitalization; causes of hospital mortality and late mortality; and health care costs. The incidence of serious adverse events related to CPR, ECMO, coronary angiography, and LV unloading will be documented as safety endpoints.

For patients still hospitalized at 30 days, bedside assessment is performed. For discharged patients, assessment is conducted during scheduled follow-up clinic visits or via structured telephone interview using validated instruments.

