### Cost-effectiveness analysis

A comprehensive cost-effectiveness analysis will be conducted from both healthcare system and societal perspectives. Data collection includes: (1) Direct medical costs**:** ECMO equipment and disposables, catheterization laboratory procedures, ICU and hospital stay, medications, rehabilitation services, and (2) Indirect costs: Lost productivity, caregiver burden (collected via structured surveys). The Outcomes of Quality-adjusted life years (QALYs) are calculated using EQ-5D-5L assessments at discharge, 3 months, 6 months, and 1 year.

Incremental cost-effectiveness ratio (ICER) will be calculated as cost per QALY gained. Sensitivity analyses will examine uncertainty in cost and outcome estimates. A willingness-to-pay threshold consistent with Taiwan's healthcare context (approximately $50,000–100,000 USD per QALY) will be used for interpretation."

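### Follow-up is counted from discharge in one place and from the arrest in another, so the timing of the 30-day CPC after early discharge is not fixed, and the 1-year EQ-5D-5L is in neither schedule

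*Protocol article*

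**What the plan says.** Four places in the protocol article bear on when outcomes are measured.

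- **Follow-up:** "All enrolled patients will be followed at hospital discharge and 1 month, 3 months, and 6 months after discharge". Survival, neurological and functional recovery, and readmission are collected at these contacts, by interview or outpatient appointment. The section refers to Fig. 2.
- **Fig. 2 legend:** "Clinical examination will be assessed at 30 days, 90 days and 180 days after cardiac arrest".
- **Study endpoints:** "The primary endpoint is defined as 30-day survival with Cerebral Performance Category (CPC) score of 1 or 2". The sentence names no time origin. On method, the section says "For patients still hospitalized at 30 days, bedside assessment is performed", and then "For discharged patients, assessment is conducted during scheduled follow-up clinic visits or via structured telephone interview using validated instruments". The secondary endpoints include "crude survival and neurologically favorable survival at discharge, 3 months, and 6 months", again without an origin.
- **Cost-effectiveness analysis:** QALYs are "calculated using EQ-5D-5L assessments at discharge, 3 months, 6 months, and 1 year".

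**The concern.** The Follow-up section and the figure it cites use different time origins. For any one patient the two schedules differ by the whole length of stay.

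This matters most for the primary endpoint. Patients still in hospital have a fixed assessment day. Patients already discharged are assessed at a scheduled visit or by telephone, with no day attached, and the only text that schedules outpatient contacts counts from discharge. With eight centers, some could work from the Follow-up text and others from the figure. Whether a patient is exposed to late assessment depends on leaving hospital before day 30, which happens after randomization.

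The 3- and 6-month secondary endpoints have the same ambiguity. Counted from discharge, the interval since arrest varies between survivors, and the time point is undefined for a patient who dies in hospital. Counted from the arrest, it is defined for everyone randomized.

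A separate gap concerns the economic analysis. It needs a utility measurement at 1 year, which neither follow-up schedule contains.

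**Working it through.** The plan gives no figure of its own to reproduce here, and the sample size does not depend on this point. The check sets the schedules side by side and works out how far apart they are.

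**Inputs.** The visit times come from the Follow-up section and the Fig. 2 legend. Months are taken as 30 days. Length of stay, L, is an assumption, because the document gives none.

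**Step 1: day after arrest of each visit.** Under the Follow-up section the visits fall on day L + 30, L + 90 and L + 180. Under the Fig. 2 legend they fall on day 30, 90 and 180 for every patient.

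| Assumed stay L (days) | 1-month visit | 3-month visit | 6-month visit |
|---|---|---|---|
| 7 | 7 + 30 = 37 | 97 | 187 |
| 14 | 14 + 30 = 44 | 104 | 194 |
| 21 | 21 + 30 = 51 | 111 | 201 |
| 29 | 29 + 30 = 59 | 119 | 209 |
| Fig. 2 legend, any L | 30 | 90 | 180 |

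If the discharge-based visit is used for the primary endpoint, the CPC is therefore taken L days late.

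**Step 2: who is affected.** Patients still in hospital at day 30 are assessed at the bedside then. Patients dead by day 30 are failures whenever a visit would have fallen. Only survivors discharged before day 30 are left, and for them only the CPC component.

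**Step 3: direction.** Late assessment can act either way.

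- Take a patient discharged on day 20, so that the visit falls on day 20 + 30 = 50. If the CPC is 3 on day 30 and improves by day 50, a failure could be scored as a success.
- If the same patient does well at day 30 but dies on day 45, no day-30 CPC may exist. The statistical analysis section counts an unassessable primary outcome as a failure, so a success could be lost.

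The document gives nothing from which to say which would be more common, or whether it would differ by arm.

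**Step 4: the 1-year measurement.** Counting 1 year as day 365 after arrest:

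- Under the Fig. 2 legend the last contact is day 180, which is 365 − 180 = 185 days short.
- Under the Follow-up section the last contact is day L + 180. For L = 7 the shortfall is 365 − 187 = 178 days. Even for an assumed stay of 60 days it is 365 − 240 = 125 days.

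Under either reading the scheduled follow-up of survival and readmission stops about 4 to 6 months before the last EQ-5D-5L.

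**The case against.** The strongest reply is that a day-30 assessment is plainly intended. The endpoint is called 30-day, the figure counts from the arrest, and the inpatient rule turns on day 30. A telephone interview is also allowed, so the assessment of a discharged patient need not wait for a clinic date. The survival component is fixed by the date of death and cannot drift with the visit. An exact window is detail that an article may leave to the full protocol.

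Most of this stands. A reader might infer that the primary endpoint as a whole would be measured at the wrong time, and differently by arm. The documents do not support that. It would require the Follow-up text to override the figure and the telephone route to go unused. It would also require a difference in length of stay between the arms, and the document gives no such difference.

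On the economic side, the cost-effectiveness section does name the 1-year EQ-5D-5L and lists its own cost data. It nowhere says that cost collection stops at 6 months. A reader might infer that utilities and costs certainly have different horizons, but that goes beyond the text.

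The reply does not remove the contradiction. An article may omit a window, but this one states two time origins, and no sentence says which applies to the CPC of a discharged patient.

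**Conclusion.** The point holds as an inconsistency to be corrected. It does not show that the primary endpoint is invalid.

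- **Time origin.** The Follow-up section and the Fig. 2 legend contradict each other by the length of stay. A site following the Follow-up section could take the 30-day CPC on day 37 to 59 for assumed stays of 7 to 29 days, and the 3- and 6-month outcomes would move by the same amount. These days illustrate the effect. They rest on assumed stays and on the discharge-based schedule being the one used.
- **Primary endpoint.** The exposure is limited to the CPC component in survivors discharged before day 30. The size of any bias cannot be derived from the document, and its direction is unknown.
- **One-year utility.** The 1-year EQ-5D-5L has no counterpart in either follow-up schedule, which both end at about 6 months. This does not depend on the assumed stay, within the range of 7 to 60 days examined.

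The correction is worth making now, because a CPC not taken at day 30 cannot be recovered after data collection.

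**What to change.** 1. **Follow-up and Study endpoints.** Count all outcome times from the arrest: days 30, 90 and 180, in agreement with the Fig. 2 legend. Visits timed from discharge may stay as care visits, provided they do not define outcome times.
2. **Day-30 CPC.** State that it is taken within a short, named window around day 30 after arrest, by bedside, clinic or telephone, whatever the discharge date.
3. **Cost-effectiveness analysis.** Align it with the follow-up schedule in one of two ways. Either add a 1-year telephone contact that collects EQ-5D-5L, vital status and resource use together, or end the QALY and cost horizon at day 180.

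Items 1 and 2 change a few sentences and leave the sample size, endpoint definition and primary analysis as they are. For item 3, the first option costs one short call per survivor, and the second gives up the 1-year horizon.
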